#### 9.4.2 ANALYSIS OF THE PRIMARY EFFICACY ENDPOINT(S)

The **primary outcome** for the study is a **post-enrollment (168 hours (7 days)) Modified Vesikari Score (MVS)**, defined as an MVS  $\geq 9$ . The post-enrollment score is calculated based on the elements of the score collected Day 0 through Day 7. Each of the seven components will be assigned a score for the entire study period (from ED disposition to Day 7). Scoring of each component is described in Table 3.0.

| Table 3.0 Modified Vesikari Scale                                       |          |                                     |                 |                      |
|-------------------------------------------------------------------------|----------|-------------------------------------|-----------------|----------------------|
| Scale Component                                                         | Score    |                                     |                 |                      |
|                                                                         | 0 Points | 1 Point                             | 2 Points        | 3 Points             |
| Diarrhea duration (hours)                                               | 0        | < 96.0                              | 96.0 – < 120.0  | $\geq 120.0$         |
| Maximum number of watery stools/24 hour period                          | 0        | 1–3                                 | 4–5             | $\geq 6$             |
| Vomiting duration (hours)                                               | 0        | < 24.0                              | 24.0 – < 48.0   | $\geq 48.0$          |
| Maximum number of vomiting episodes/24 hour period                      | 0        | 1                                   | 2–4             | $\geq 5$             |
| Maximum recorded rectal temperature ( $^{\circ}\text{C}$ ) † | <37.0    | 37.0 – < 38.5                       | 38.5 – < 39.0   | $\geq 39.0$          |
| Unscheduled health care visit                                           | None     | NA                                  | Primary care    | Emergency department |
| Treatment                                                               | None     | Rehydration with intravenous fluids | Hospitalization | NA                   |

†Temperatures are adjusted for the location of measurement: 1.1 $^{\circ}\text{C}$  was added to axillary temperatures and 0.6 $^{\circ}\text{C}$  was added to oral temperatures

The components will be calculated by the following rules:

1. **Maximum number of episodes of vomiting in a 24-hour period:** The number of episodes (defined as per the protocol) of vomiting will be collected in 24-hour blocks.
2. **Maximum number of episodes of diarrhea (watery stools) in a 24-hour period:** The number of episodes (defined as per the protocol) of diarrhea will be collected in 24-hour blocks.
3. **Maximum recorded rectal temperature:** The maximal temperature will be collected in 24-hour blocks. The method of measurement will be collected (e.g. temporal, rectal, oral) and the temperature obtained will be adjusted to a rectal temperature as per Table 3.0.

4. **Vomiting duration:** This is calculated as the time between ED disposition and the last vomiting episode. When vomiting is reported to have stopped on study questionnaires, and started again on a later report, but prior to all symptoms (i.e. vomiting and diarrhea) stopping, the vomiting is considered to have continued throughout that time-period. The vomiting episode would thus be calculated from ED disposition date/time until the final vomiting stop date/time. If there is a period of 24 hours without vomiting and without diarrhea, then the episode would be considered to have ended and symptoms reported after that period would not be included in the calculation.
5. **Diarrhea duration:** This component will be calculated using exactly the same procedure described for vomiting when diarrhea is present at randomization. If diarrhea is not present at randomization and never occurs, diarrhea duration will be 0. If diarrhea starts after randomization but prior to a 24 hour period without vomiting, the start time will be calculated from the reported start time and the end time will be computed as described for vomiting duration. Specifically, if there is a period of 24 hours without vomiting and without diarrhea then the episode would be considered to have ended and symptoms reported after that period would not be included in the calculation.
6. **Unscheduled healthcare visit:** Presence of an unscheduled healthcare visit will be collected on the questionnaire and will be classified as “none”, “primary care”, or “emergency department”. All revisits to the participating site are verified by database review.
7. **Treatment:** Treatment will be classified as “none”, “intravenous rehydration”, or “hospital admission”. If the participant is admitted directly following their enrollment ED visit and that admission stay is longer than 48 hours, it will be counted as treatment in the post enrollment MVS. If the participant’s enrollment admission stay was less than 48 hours, it will not be counted as “treatment”.

Data needed to calculate the MVS will be collected at Enrollment (Day 0), on the 24, 48, and 168 hour questionnaires, and verified using chart review performed within 37 days of participant enrollment. The primary outcome will be tabulated by treatment for each site and weight stratum. A Mantel-Haenszel statistic, assessing the effect of treatment on the primary outcome controlling for strata, will be calculated to test the primary hypothesis. Summary statistics for the effect sizes will be given. Choice of final summary statistic reported (e.g. risk difference, risk ratio, or odds ratio) will be based, in part, by which statistic is least variable across subgroups (i.e. shows the smallest degree of interaction across subgroups). It is expected that the asymptotic version of the Mantel-Haenszel test will be appropriate for the final analysis. In the case of low outcome counts, the Mantel-Fleiss criterion will be assessed. If the criterion has a value less than 5, the exact version of the Mantel-Haenszel test will be used and the two-sided p-value will be defined as the sum of all probabilities of test statistics with point probabilities less than or equal to that of the observed value. In the event any patients were randomized within an incorrect stratum due to misspecification at time of randomization, the actual, rather than assigned category will be used in the above analysis.

Although randomization should result in approximate balance between treatment arms with respect to critical baseline variables affecting the outcomes, additional exploratory analyses will be conducted to assess the effects of treatment after adjusting for baseline covariates in models for the primary outcome.

The covariates considered are:

- Baseline MVS (actual score)
- Duration of symptoms prior to enrollment (<48 hours vs. 48 hours or more)
- Age
- Gender
- Clinical center

- Antibiotic usage during the 14 days prior to ED visit
- Severity of baseline diarrhea and vomiting
- Hydration assessment
- Need for hospitalization at index visit

---

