**What if at baseline the pre-enrollment MVS is  $\geq 9$ ?** Regardless of the score assigned at Time 0 (i.e. *pre-enrollment score*), EVERYONE reverts to a score of 0 at enrollment (i.e. the study evaluates the impact on the disease process going forward). The *pre-enrollment score*, which is based on symptoms prior to presentation, will serve as a covariate in a secondary analysis of the primary outcome and will be employed for sub-analysis purposes. **The primary outcome (the presence of moderate-severe disease, as defined by a MVS of  $\geq 9$  during the 7 day follow-up period) will ONLY include symptoms and outcomes that occur following the ED visit (i.e. after enrollment) and will not be directly impacted by the pre-enrollment score.**

**Why a cut-point of 9?** With the original score, severe disease was defined as  $\geq 11$ ; moderate as  $\geq 9$ . In our derivation study, construct validity was proven by using scores of  $\geq 9$  to define moderate and  $\geq 11$  to define severe disease. These cut-points were associated with significant increases in other measures of disease severity [e.g. daycare ( $P=0.01$ ) and work absenteeism ( $P=0.002$ )].

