### 9.2 SAMPLE SIZE DETERMINATION

The primary analysis will be performed on a binary outcome: Development of moderate-to-severe disease. The power of this analysis is based on the proportion of patients with moderate-to-severe disease. Our pilot data indicate that 30% of patients will have moderate to severe disease following the index visit (personal communication with [name]). Furthermore, expert surveys indicated that an absolute risk reduction of 10% would constitute a minimal clinically-important difference (MCID). Therefore, our sample size calculation assumed a 30% event rate in the control group for which we desire to detect an absolute beneficial treatment effect of 10% with 90% power. Using a two-sided type I error of 0.05 and the hypothesized proportions yields a required total sample size of 784 patients. Our expected power, should we find different event rates in our 2 groups, is displayed in Table 2.0.

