### 9.4.6 PLANNED INTERIM ANALYSES

As per the DSMB charter, no interim analysis will be performed for the DOSE-AGE study. In the case that an interim analysis is to take place, it will be done in accordance with the DSMB charter. We will also make the appropriate adjustments to the significance level and update the study Statistical Analysis Plan.

Early stopping for efficacy and futility will not be considered due to concerns for overestimating or underestimating treatment effects. The DSMB will, in collaboration with the trial steering committee, establish safety stopping rules prior to trial initiation.

Data center biostatisticians involved in this study will be partially blinded, aware of results by treatment arm, but not of arm identities. Other data center personnel will be blinded to treatment assignments, however the data center study team for this trial will have access to individual safety and efficacy data. Personnel at the clinical centers will be blinded to aggregate safety and efficacy data until the time of final analysis or until the decision is made to unblind all investigators to study results.

All by-treatment interim analyses will refer to arms as “A” and “B” throughout the report presented to the DSMB. The DSMB will have the option of being unblinded to treatment arm identity at any time.

For additional information about safety stopping rules, reference the DSMB charter.

---

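### The primary effect measure is not named in advance: Section 9.4.2 picks it partly by which scale varies least across subgroups, although the trial is sized on a 10-point risk difference

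*Combined protocol and SAP*

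**What the plan says.** **Section 9.4.2 (primary analysis).** The outcome is tabulated by treatment for each site and weight stratum. The test is fixed: "A Mantel-Haenszel statistic, assessing the effect of treatment on the primary outcome controlling for strata, will be calculated to test the primary hypothesis". On estimation it says: "Summary statistics for the effect sizes will be given". It then adds a selection rule. Three candidate measures are offered and none is preferred; which one becomes the reported summary "will be based, in part, by which statistic is least variable across subgroups". A parenthesis explains that this means the smallest degree of interaction across subgroups.

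**Section 9.2 (sample size).** The target is absolute: "expert surveys indicated that an absolute risk reduction of 10% would constitute a minimal clinically-important difference (MCID"), and "our sample size calculation assumed a 30% event rate in the control group". Table 2.0 lists power by absolute difference.

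**Section 9.4.1 (general approach).** A 95% confidence interval is promised for the primary treatment effect; its scale is not given.

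**Section 9.4.6 (interim analyses).** "Data center biostatisticians involved in this study will be partially blinded, aware of results by treatment arm, but not of arm identities".

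**Section 9.4.7 (subgroups).** Four factors are listed: sex, age, vomiting frequency and diarrhea. Section 9.4.2 does not say whether its subgroups are these or the site-by-weight strata.

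**The concern.** This is a stated rule, not only a gap. It makes the headline estimate depend on the data that it summarises.

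The rule also cannot be reproduced as written. The subgroups are undefined, no measure of variability is given, and the words *in part* leave the rest of the criterion unstated. Two statisticians could both follow the text and report different primary estimates.

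What is at stake is interpretation. Readers will want to set the estimate and interval beside the 10-point difference that justified the trial. If the rule selects a ratio, the plan does not oblige anyone to report the risk difference with its interval.

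**Working it through.** **1. Reproduce the plan's own figure.** Inputs from Section 9.2: control risk 0.30, intervention risk 0.20, two-sided alpha 0.05, power 0.90. Allocation is 1:1 (Section 6.3). With mean risk 0.25:

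n per arm = [1.960 × √(2 × 0.25 × 0.75) + 1.2816 × √(0.30 × 0.70 + 0.20 × 0.80)]² / 0.10²
= [1.2002 + 0.7795]² / 0.01 = 391.9, rounded up to 392.

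The total is 784, as stated. The design was therefore worked on absolute risks, and naming a risk difference changes neither the 784 nor the 1030.

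**2. Do the three measures carry the same information?** At the design point:

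- Risk difference (RD) = 0.30 − 0.20 = 0.10
- Risk ratio (RR) = 0.20/0.30 = 0.667
- Odds ratio (OR) = (0.20/0.80)/(0.30/0.70) = 0.583

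They correspond only at a control risk of 30%. Holding each ratio fixed and changing the control risk p gives RD = p × (1 − 0.667) for the risk ratio. For the odds ratio, RD = p − o/(1 + o), with o = 0.583 × p/(1 − p).

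| Control risk | RD implied by RR 0.667 | RD implied by OR 0.583 |
|---|---|---|
| 20% | 0.067 | 0.073 |
| 25% | 0.083 | 0.087 |
| 30% | 0.100 | 0.100 |
| 35% | 0.117 | 0.111 |
| 40% | 0.133 | 0.120 |

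A ratio reported alone does not show whether the absolute reduction reached 10 points.

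**3. How well would the rule identify the right scale?** The plan does not define the rule fully, so this part rests on assumptions: equal-sized subgroups, the scale with the smallest Cochran Q chosen, and 927 evaluable children (1030 × 0.90, from the plan's 10% loss to follow-up). The subgroup counts are also assumed. Twelve matches the 6 sites × 2 weight bands.

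| Truth: RD constant at 10 points, control risks 20–40% | RD chosen in about |
|---|---|
| 4 subgroups | 64% |
| 6 subgroups | 57% |
| 12 subgroups | 35% |

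The 12-subgroup figure is the least stable, because each subgroup has only about 39 children per arm (927/24). Rerunning it with three ways of handling small cells gave about 26% (half added to each cell for the ratio measures only), 37% (half added only where a cell was empty) and 42% (half added to every cell for all measures).

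As a reference case, take a control risk of 30% in every one of 4 subgroups and the same effect in each. All three scales are then constant and there is no right answer. The rule chose RD in about 45–47% of trials, RR in about 51–52% and OR in about 3%, at 784 or 927 evaluable.

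**The case against.** The strongest reply is that inference is safe and nothing is lost. The Mantel-Haenszel test does not depend on the measure reported, so its p-value, type I error and power stand. Section 9.4.2 also promises a tabulation by treatment within strata and effect-size summaries in the plural, from which crude and stratified risk differences can be computed. Seeking a scale with little interaction is a recognised aim. All of this stands. It narrows the point to the choice of headline estimate and interval. It does not remove it, because permitting a risk difference is not committing to one, and the aim is sound only when the scale is settled beforehand.

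The simulation is also open to challenge: subgroup number, control-risk spread and metric are not in the plan. That is fair. With 4 or 6 subgroups the rule does better than the one-in-three of a blind pick, so calling it pure noise would go too far. Part of the odds ratio's low share comes from its lying between the other two scales.

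A reader might infer more than the documents support:

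- *That the choice is made on unblinded data.* Section 9.4.6 keeps arm identities masked. The statisticians do see results by arm, so the choice still uses outcome data.
- *That the trial could not show whether 10 points was reached.* The tabulated counts supply the information; only the commitment is missing.
- *That success is formally judged against 10 points.* Section 9.2 uses that figure for sample size, and no section sets a decision rule on it.
- *That the primary estimate must adjust for pre-enrollment severity.* Section 3 says that score "will serve as a covariate in a secondary analysis of the primary outcome", so adjustment is already planned. Making it primary is a separate preference whose gain depends on an association that the documents do not quantify.

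Finally, Sections 9.4.6 and 9.4.9 refer to a study SAP. No SAP text apart from Section 9 was available, so whether one names the measure could not be checked.

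**Conclusion.** The point holds for Section 9.4.2 as written. The primary effect measure is left to a partly specified, data-dependent rule, while the important difference and the sample size are absolute. The test, alpha, power and N are sound.

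The size of the problem can only be illustrated. Under the stated assumptions, a truly constant 10-point risk difference would be reported on its own scale in roughly 35–64% of trials, with the lower end sensitive to small-cell handling. The conclusion does not depend on those percentages. It follows from the text, which selects the headline estimate after outcome data by arm are known and nowhere commits to a risk difference with a confidence interval.

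This is worth correcting because correction is nearly free, but it is not a threat to the validity of the primary test.

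**What to change.** Before unblinding, and preferably before any outcome results by arm are reviewed, replace the selection sentence in Section 9.4.2 with wording to this effect:

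*The primary effect measure is the Mantel-Haenszel risk difference stratified by site and weight, with its 95% confidence interval, interpreted against the 10-point minimal clinically important difference. The risk ratio and odds ratio, with 95% confidence intervals, are supportive only.*

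Keep the stratified Mantel-Haenszel test as the primary test, including its exact version for low counts. State in Section 9.4.1 that the primary confidence interval is on the risk-difference scale. If a separate SAP already names a measure, reconcile the two texts.

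The cost is a wording amendment: no new data, and no change to the 784 evaluable or 1030 randomized, to alpha, or to the power of the planned test.

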#### 9.4.3 ANALYSIS OF THE SECONDARY ENDPOINT(S)

**Secondary outcomes** and how they will be assessed can be found below:

1. **Frequency of vomiting from study enrollment to day 7:** The total number of episodes of vomiting and diarrhea related to the presenting illness will be compared between groups (active and placebo). This data will be obtained from the study questionnaires performed on Day 0, 24, 48, and 168 (7 days) hours after enrollment. Questionnaires (telephone or email) will contain questions regarding vomiting presence, number of episodes, and vomiting cessation date and time. Frequency will be defined as the total number of episodes across the study duration and will not consider differences in the vomiting duration across participants.
2. **Duration of vomiting:** The total number of days the participant experiences vomiting from Day 0 to Day 7. This data will be obtained from the study questionnaires performed on Day 0, 24, 48, and 168 (7 days) hours after enrollment. Questionnaires (telephone or email) will contain questions regarding vomiting presence, number of episodes, and vomiting cessation date and time. A participant with a 24-hour break in symptoms will be assumed to have ceased vomiting.
3. **Proportion of participants who experience vomiting within 7 days of enrollment:** The proportion of participants will be determined using data from the participant questionnaires performed 24, 48, and 168 hours after enrollment (Time 0).
4. **Proportion of participants who require an unscheduled health care provider visit within 7 days of enrollment:** Return visits for unscheduled care to a health care provider related to vomiting, diarrhea, dehydration, fever, abdominal pain, or fluid refusal within 7 days, not including scheduled visits (e.g. reassessments, vaccinations, etc.) will also be measured using follow up questionnaires 24, 48, and 168 hours after enrollment. Return to care data will be confirmed by reviewing the participant's hospital chart. Not all data within a patient's medical record will be available to the research team therefore the questionnaires will be the primary source of this data.
5. **Proportion of participants who require intravenous rehydration:** If the participant required an unscheduled health care visit (see #4 above), the participant will be asked additional questions related to intravenous (IV) insertion, treatment course, and disposition. Intravenous fluids administered at the index visit will not be included as part of this outcome.
6. **Caregiver satisfaction as measured by a 5-point Likert scale in the 48 hours following ED disposition:** Caregiver satisfaction with the therapy provided (oral ondansetron or placebo) in the 48 hours following ED disposition. This will be measured using a 5 point Likert scale on the questionnaire administered 168 hours after Time 0.

The analysis of secondary outcomes will be undertaken as detailed below:

1. **Frequency of vomiting from study enrollment to Day 7:** The total number of episodes of vomiting and diarrhea related to the presenting illness will be compared between groups (active and placebo) using a generalized linear model to compare differences between Poisson rates whilst adjusting for stratification.

2. **Duration of vomiting :** The total number of days the participant experiences vomiting from Day 0 to Day 7 will be compared using the Van Elteren test, stratified by center and duration of symptoms (pre-enrollment). If a number of patients still experience symptoms at the 7-day follow-up questionnaire, this will be tested using a suitable procedure to take account of censoring such as median regression or additive hazard models. Additional analyses involving this outcome will include linear regression models that adjust for possible effects of baseline characteristics.
3. **Proportion of participants who experience vomiting within 7 days of enrollment:** The proportion of participants with vomiting following enrollment will be compared using Mantel-Haenszel test stratified by site and weight.
4. **Proportion of participants who require an unscheduled health care provider visit within 7 days of enrollment:** The proportion of participants who require an unscheduled health care provider visit within 7 days of enrollment will be compared using Mantel-Haenszel test stratified by site and weight.
5. **Proportion of participants who receive intravenous rehydration:** The proportion of participants who receive intravenous rehydration will be compared using Mantel-Haenszel test stratified by site and weight. If the number of participants requiring intravenous rehydration is low then exact calculations without stratification may be required.
6. **Caregiver satisfaction as measured by a 5-point Likert scale in the 48 hours following ED disposition:** Caregiver satisfaction with the therapy provided (oral ondansetron or placebo) in the 48 hours following ED disposition will be compared using a Mann-Whitney U Test.

---

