A recent small study found that 24% of pediatric patients who were treated with a single dose of ondansetron for acute gastroenteritis in the ED reported experiencing recurrent emesis within 24 hours of discharge. We hypothesize that the use of a physician-dispensed, as needed home dosing regimen of ondansetron given to patients (in anticipation of recurrent emesis and risk of dehydration) may prevent a return to the ED. While a small 2010 study found no reduction in ED revisits after discharging patients’ home with a written prescription for ondansetron, the authors caution that they did not track the number of patients who actually filled their prescriptions. In 2002, Ramsook et al. conducted a single-centre, double-blinded, placebo-controlled trial involving 145 children, comparing six doses of ondansetron/placebo administered every 8 hours for two days (scheduled). Vomiting was reduced after the first dose was administered; however, no further benefit was seen following discharge (vomiting occurred in 42% administered ondansetron versus 46% administered placebo at 24 hours). In addition, at the 24 hour and 48 hour follow-ups, the median number of vomiting episodes remained zero, with no statistically significant difference between groups. During the 48 hours following ED discharge, children administered ondansetron had threefold more diarrhea than those in the placebo group (mean 7.7 versus 2.3 episodes). The revisit rate was also higher in the ondansetron group ( $P=0.05$ ). Of the four patients with revisits in the ondansetron arm, two returned with persistent vomiting and the other two with persistent diarrhea. Interestingly, providing a home dose of ondansetron to patients by the ED physician as part of discharge planning may/ promote compliance on an outpatient basis.

A second double-blinded, placebo-controlled trial of relevance was published by Yilmaz et al. in 2010, in which the authors provided participants ( $N=109$ ) with ondansetron/placebo every 8 hours for a total of 24 hours. In this study, although ondansetron administration reduced the frequency of vomiting following discharge (mean of 1.7 versus 0.2 episodes over 24 h;  $P<0.001$ ), its administration was also associated with an increase in the number of

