| 
Among children receiving active treatment versus placebo:
 
(1) Is there a difference in the (a) duration of vomiting, (b) frequency of vomiting, or (c) the proportion who experience vomiting following ED disposition.
 
(2) Is there a difference in the proportion who require an unscheduled health care provider visit?
 
(3) Is there a difference in the proportion who require intravenous rehydration?
 
(4) Is there a difference in the satisfaction with care?
 | 
1. Vomiting: Frequency, Duration, Proportion
 
2. Health Care Use: ED, Primary Care
 
3. Intravenous rehydration
 
4. Caregiver Satisfaction with Therapy Provided: Likert Scale
                                                                              |                                                                                                                        |
| Safety                                                                                                                                                                                                                                                                                                                                                                                                                                                                                                  |                                                                                                                                                                                                                                                                                     |                                                                                                                        |

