## 9.4 STATISTICAL ANALYSES

### 9.4.1 GENERAL APPROACH

For the primary outcome, the significance level will be set at 0.05. The overall significance level for statistical tests on the secondary outcomes will be set at 0.05.

To control the overall significance level for the secondary outcomes, the significance level will be adjusted for multiple comparisons. Vomiting and diarrhea duration, vomiting and diarrhea frequency, proportion with vomiting, unscheduled healthcare provider visits, intravenous rehydration, and caregiver satisfaction will be subject to Holm's stepdown procedure. Specifically, the smallest of the eight p-values will be compared to a significance level of  $0.05/8$ . If significance is reached, the next-smallest p-value will be compared to  $0.05/7$ , and so on. The final p-value of the six will be compared to 0.05, assuming that all others are significant. Confirmatory and tertiary outcome results will not be adjusted for multiple comparisons, as these are more exploratory in nature.

A 95% confidence interval will be reported around estimates of the treatment effects of the primary and secondary outcomes.

All analytical models will be evaluated and adjustments will be made if any assumptions appear to be seriously violated.

Publication of the primary results will include reporting of key baseline characteristics overall, and by assigned treatment arm (active or placebo). These will include, but will not be limited to,

- Gender
- Age
- Season
- Weight

- Primary care physician access
- Daycare attendance
- Receipt of rotavirus vaccine
- Vomiting and diarrhea duration and frequency
- Presence of fever
- Prior ED visits, IV rehydration, hospitalization
- Baseline MVS
- Duration of symptoms prior to enrollment (<48 hours vs. 48 hours or more)
- Antibiotic usage during the 14 days prior to ED visit
- Hydration assessment (Clinical Dehydration Scale score)
- Need for hospitalization from initial ED visit

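### The vomiting-frequency outcome in 9.4.3 is written as one total of vomiting and diarrhea episodes, contradicting its label, objective 1(b) and the eight-test Holm family; read literally, it dilutes a vomiting benefit

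*Combined protocol and SAP*

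**What the plan says.** Secondary objective 1 in Table 1.0 (and in the Synopsis) asks about "a) duration of vomiting, (b) frequency of vomiting, or (c) the proportion who experience vomiting following ED disposition". Diarrhea is not part of it.

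Section 9.4.3 has two numbered lists, one defining the secondary outcomes and one giving their analyses. Item 1 in each carries a vomiting-frequency label and a window from enrollment to Day 7. Under that label the definition reads "The total number of episodes of vomiting and diarrhea related to the presenting illness will be compared between groups (active and placebo". The analysis repeats the phrase and adds the model: "The total number of episodes of vomiting and diarrhea related to the presenting illness will be compared between groups (active and placebo) using" then "a generalized linear model to compare differences between Poisson rates whilst adjusting for stratification". Yet the definition says of the questionnaires that supply the data that they "will contain questions regarding vomiting presence, number of episodes, and vomiting cessation date and time".

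Section 9.4.1 places these outcomes under Holm's procedure: "Vomiting and diarrhea duration, vomiting and diarrhea frequency, proportion with vomiting, unscheduled healthcare provider visits, intravenous rehydration, and caregiver satisfaction". It counts eight p-values and starts at 0.05/8.

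Section 9.4.4 separately analyses diarrhea episodes as a safety outcome over the 48 hours after ED disposition. Section 9.4.2 has vomiting and diarrhea episodes collected as separate counts in 24-hour blocks.

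**The concern.** Item 1 is the only analysis that could answer objective 1(b), and as written it does not measure vomiting frequency. For this drug the mismatch matters because the protocol expects the two symptoms to move in opposite directions. The study rationale mentions associations with more diarrhea, and section 4.2 sets possible benefit against a possible rise in diarrhea frequency. The Background reports such a rise in both earlier home-dosing trials; for one of them, "children administered ondansetron had threefold more diarrhea than those in the placebo group (mean 7.7 versus 2.3 episodes".

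A total of the two counts nets the intended benefit against the anticipated harm. A true fall in vomiting would be understated, and with a modest fall the sign could turn. The text also leaves room for two analysts to compute different outcomes under one name, which should not be left open for a multiplicity-controlled endpoint.

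**Working it through.** **1. The plan's own count of tests.** Taking each symptom separately, the 9.4.1 list gives: vomiting duration, diarrhea duration, vomiting frequency, diarrhea frequency, proportion vomiting, unscheduled visits, intravenous rehydration, satisfaction = 8. This reproduces the 0.05/8 starting level. If frequency is one combined test the list gives 7; if duration is combined as well, 6. The thresholds therefore require vomiting frequency and diarrhea frequency to be separate tests, whereas 9.4.3 describes one. (The paragraph's closing sentence speaks of six p-values, so 9.4.1 is not fully consistent either.)

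**2. The texts side by side.**
- Objective 1(b): vomiting.
- Label of item 1, both lists: vomiting.
- Data items named in the definition: vomiting.
- Holm family: vomiting and diarrhea, as two tests.
- Count defined and modelled in item 1: vomiting and diarrhea, as one total.

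Only the last treats them as one quantity, but it is the operative specification and it appears twice.

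**3. Effect of the literal reading.** Inputs are the means that section 2.2 cites from the earlier trial that dosed every 8 hours for 24 hours. The assignment to arms follows the text's statements that ondansetron reduced vomiting and increased diarrhea.
- Vomiting over 24 h: placebo 1.7, ondansetron 0.2. Difference 0.2 − 1.7 = −1.5; ratio 0.2/1.7 = 0.12.
- Diarrhea: placebo 4.3, ondansetron 5.0. Difference +0.7; ratio 5.0/4.3 = 1.16.
- Combined: placebo 1.7 + 4.3 = 6.0; ondansetron 0.2 + 5.0 = 5.2. Difference −0.8; ratio 5.2/6.0 = 0.87.
- Share of the absolute benefit lost: 0.7/1.5 = 47%. An 88% relative reduction becomes 13%.

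**4. Break-even.** Keep the placebo means and diarrhea at 5.0 on ondansetron. The combined ratio is 1 when vomiting falls by exactly 0.7 episodes: 0.7/1.7 = 41%. A smaller fall gives a ratio above 1. For an assumed fall from 1.7 to 1.2 (29%), the totals are 6.2 against 6.0, ratio 1.03.

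**5. Effect on power, as a range.** The plan gives no power for this outcome. I use 392 per arm, half the 784 in section 9.2. That figure reproduces for the primary outcome: [1.96·√(2·0.25·0.75) + 1.2816·√(0.3·0.7 + 0.2·0.8)]² / 0.1² = 392. For a log rate ratio, take the variance per arm as (1/mean + φ)/392, where φ is an overdispersion value I assume. With means 6.0 and 5.2 and φ = 1, the standard error is √[(1/6.0 + 1 + 1/5.2 + 1)/392] = 0.0776, |ln 0.867| = 0.143, z = 1.84, and power at 0.05 is 0.45. Across the range:
- Combined count, φ = 0, 0.5, 1, 2: power 0.997, 0.68, 0.45, 0.27.
- Vomiting only (1.7 against 0.2): about 1.0 for every φ from 0 to 2.

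**The case against.** The strongest reply is that this is a drafting slip, and that nobody means to add stools to vomits. The label, the vomiting-only data items and the eight-test Holm family all support that. This part stands: a reader might infer from 9.4.3 that a summed outcome is the settled plan, and the documents do not establish it. What they establish is a contradiction. It still needs correcting, because the combined phrase appears in both the definition and the model statement, and no vomiting-only count is specified elsewhere.

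A reader might also infer that the cited evidence shows the total reading as no effect or as harm. It does not. The 24-hour trial gives dilution: a ratio of 0.87 is still a benefit. For the six-dose trial, a reader might take the diarrhea difference, 7.7 − 2.3 = 5.4, as the change in the total. That cannot be derived: the Background gives its vomiting only as percentages and medians, and a median difference cannot be added to a difference in means. It also reports no further vomiting benefit after discharge in that trial, so there is no benefit there to be masked.

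Finally, the damage is limited. Vomiting is also tested as duration and as a proportion, diarrhea has its own safety analyses, and the counts are collected separately, so nothing is lost. That bears on how serious the point is, not on whether the text is wrong.

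**Conclusion.** The point holds as a contradiction within the plan with a definite consequence if followed literally. Item 1 of 9.4.3 conflicts with its own label, its listed data, objective 1(b) and the Holm count in 9.4.1, and objective 1(b) is left without an analysis that answers it.

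On the cited 24-hour trial's means, the literal reading moves the ratio from 0.12 to 0.87 and loses 47% of the absolute benefit. A null result or wrong sign is conditional: it needs a vomiting reduction of about 41% or less, with the same placebo means and diarrhea at 5.0, and such a reduction is an assumption, not a figure from the documents.

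The arithmetic rests on means from a shorter period than the seven days here. The Background states 24 h for vomiting but gives no window for that trial's diarrhea counts; I took them as comparable. The power range rests on the assumed φ.

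The primary outcome and the sample sizes of 784 and 1030 are not affected.

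**What to change.** - In item 1 of both lists in 9.4.3, remove diarrhea so that the outcome and the model cover vomiting episodes only. Keep the stated window, enrollment to Day 7. Table 1.0 speaks of the period after ED disposition; any change of start point should be a separate, stated decision.
- Align 9.4.1 in one of two ways. Either define Day 0 to Day 7 diarrhea frequency as its own outcome with its own analysis in 9.4.3, or remove it from the Holm family and recount. The 48-hour safety analysis in 9.4.4 does not fill this place, because its window differs. Removing diarrhea frequency alone leaves 8 − 1 = 7 tests. Diarrhea duration is also listed without an analysis in 9.4.3; removing both leaves 6, matching the six outcomes there. Correct the closing sentence of the Holm paragraph to whichever number results.

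The cost is a short text amendment to 9.4.3 and 9.4.1, best made before any unblinded analysis. No new data are needed, since 9.4.2 already has the two symptoms counted separately.
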